# Background and Introduction

COVID-19 (previously termed as 2019-nCoV), a novel coronavirus disease with high mortality, emerges as a pandemic disease^[[1]](#endnote-1)^. In December 2019, a series of acute atypical respiratory disease occurred in Wuhan, China. This rapidly spread from Wuhan to other areas. It was soon discovered that a novel coronavirus was responsible. The novel coronavirus was named as the severe acute respiratory syndrome coronavirus-2 (SARS-CoV-2, 2019-nCoV) due to its high homology (~80%) to SARS-CoV, which caused acute respiratory distress syndrome (ARDS) and high mortality during 2002–2003^[[2]](#endnote-2)^

The disease caused by this virus was called Coronavirus disease 19 (COVID-19) and a pandemic was declared by the World Health Organization (WHO). COVID-19 has been impacting a large number of people worldwide, being reported in more than 200 countries and territories.

SARS-CoV-2 virus primarily affects the respiratory system, although other organ systems are also involved. Lower respiratory tract infection related symptoms including fever, dry cough and dyspnea were reported in the initial case series from Wuhan, China^[[3]](#endnote-3)^. In addition, headache, dizziness, generalized weakness, vomiting and diarrhea were observed^[[4]](#endnote-4)^. It is now widely recognized that respiratory symptoms of COVID-19 are extremely heterogeneous, ranging from minimal symptoms to significant hypoxia with ARDS. In the report from Wuhan mentioned above, the time between the onset of symptoms and the development of ARDS was as short as 9 days, suggesting that the respiratory symptoms could progress rapidly. This disease could be also fatal. A growing number of patients with severe diseases have continued to succumb worldwide. Epidemiological studies have shown that mortalities are higher in elder population^[[5]](#endnote-5)^ and the incidence is much lower in children^[[6]](#endnote-6)^,^[[7]](#endnote-7)^.

Current medical management is largely supportive with no targeted therapy available. More treatment modalities are being tested in clinical trials in many countries. A large number of countries have implemented physical distancing and lockdown to mitigate further spread of the virus.

# Symptomatology and Pathophysiology of the disease:

Below table gives an overview of classification of COVID 19 patients:

| TYPE | PRESENTATION |
| --- | --- |
| Asymptomatic | COVID nucleic acid test positive. Without any clinical symptoms and signs and the chest imaging is normal |
| Mild | Symptoms of acute upper respiratory tract infection (fever, fatigue, myalgia, cough, sore throat, runny nose, sneezing) or digestive symptoms (nausea, vomiting, abdominal pain, diarrhea) |
| Moderate | Pneumonia (frequent fever, cough) with no obvious hypoxemia, chest CT with lesions. |
| Severe | Pneumonia with hypoxemia (SpO2 < 92%) |
| Critical | Acute respiratory distress syndrome (ARDS), may have shock, encephalopathy, myocardial injury, heart failure, coagulation dysfunction and acute kidney injury. |

Coronaviruses are enveloped, positive-sense, single-stranded RNA viruses of ~30 kb. They infect a wide variety of host species^[[8]](#endnote-8)^. They are largely divided into four genera; α, β, γ, and δ based on their genomic structure. α and β coronaviruses infect only mammals^[[9]](#endnote-9)^. Human coronaviruses such as 229E and NL63 are responsible for common cold and croup and belong to α coronavirus. In contrast, SARS-CoV, Middle East respiratory syndrome coronavirus (MERS-CoV) and SARS-CoV-2 are classified to β coronaviruses.

The life cycle of the virus with the host consists of the following 5 steps: attachment, penetration, biosynthesis, maturation and release. Once viruses bind to host receptors (attachment), they enter host cells through endocytosis or membrane fusion (penetration). Once viral contents are released inside the host cells, viral RNA enters the nucleus for replication. Viral mRNA is used to make viral proteins (biosynthesis). Then, new viral particles are made (maturation) and released. Coronaviruses consist of four structural proteins; Spike (S), membrane (M), envelop (E) and nucleocapsid (N)^[[10]](#endnote-10)^. Spike is composed of a transmembrane trimetric glycoprotein protruding from the viral surface, which determines the diversity of coronaviruses and host tropism. Spike comprises two functional subunits; S_1_ subunit is responsible for binding to the host cell receptor and S_2_subunit is for the fusion of the viral and cellular membranes. Angiotensin converting enzyme 2 (ACE2) was identified as a functional receptor for SARS-CoV^[[11]](#endnote-11)^. Structural and functional analysis showed that the spike for SARS-CoV-2 also bound to ACE2. ACE2 expression was high in lung, heart, ileum, kidney and bladder^[[12]](#endnote-12)^. In lung, ACE2 was highly expressed on lung epithelial cells.

The symptom of patients infected with SARS-CoV-2 ranges from minimal symptoms to severe respiratory failure with multiple organ failure. On Computerized tomography (CT) scan, the characteristic pulmonary ground glass opacification can be seen even in asymptomatic patients^[[13]](#endnote-13)^. Because ACE2 is highly expressed on the apical side of lung epithelial cells in the alveolar space^[[14]](#endnote-14)^,^[[15]](#endnote-15)^, this virus can likely enter and destroy them. This matches with the fact that the early lung injury was often seen in the distal airway. Epithelial cells, alveolar macrophages and dendritic cells (DCs) are three main components for innate immunity in the airway^[[16]](#endnote-16)^. DCs reside underneath the epithelium. Macrophages are located at the apical side of the epithelium. DCs and macrophages serve as innate immune cells to fight against viruses till adaptive immunity is involved.

Immunological studies were mainly reported in severe COVID-19 patients. Patients with severe diseases showed lymphopenia, particularly the reduction in peripheral blood T cells. Patients with severe diseases were reported to have increased plasma concentrations of proinflammatory cytokines, including interleukin (IL)-6, IL-10, granulocyte-colony stimulating factor (G-CSF), monocyte chemoattractant protein 1 (MCP1), macrophage inflammatory protein (MIP)1α, and tumor necrosis factor (TNF)-α. The more severe conditions patients were in, the higher their IL-6 levels were. CD4^+^ and CD8^+^ T cells were activated in those patients as suggested by higher expression of CD69, CD38 and CD44. Higher percentage of checkpoint receptor Tm3^+^PD-1^+^ subsets in CD4^+^ and CD8^+^ T cells showed that T cells were also exhausted. NK group 2 member A (NKG2A), another marker for exhaustion was elevated on CD8+ T cells. Exhaustion of T cells could have led to the progression of the disease. Another interesting finding was that aberrant pathogenic CD4^+^ T cells with co-expressing interferon (IFN)-γ and granulocyte-macrophage colony-stimulating factor (GM-CSF) were seen in COVID-19 patients with severe disease.^[[17]](#endnote-17)^,^[[18]](#endnote-18)^

# Investigational Product:

The IP (named collectively for IP1 and IP2 combined) contains herbal holistic (full-spectrum) extracts (blend of water and CO_2_ extracts) of *Shunthi* *(Zingiber officinale* (Ginger), *Vidanga (Embelia ribes), Yashtimadhu (Glycyrrhiza glabra), Haritaki (Terminalia chebula), Guduchi (Tinospora cordifolia), Shatavari (Asparagus racemosus), Aamalaki (Emblica officinalis), Pippali (Piper longum)* and calcined zinc, *shankha bhasma.*

Following actives will be measured by corresponding method of analysis:

| **Name of the herb** | **Actives** | **Method of analysis** |
| --- | --- | --- |
| *Terminalia chebula* Extract | Tannin | UV-Vis Spectroscopy |
| *Emblica officinalis* Extract | Tannin, Total polyphenol | UV-Vis Spectroscopy |
| *Glycyrrhiza glabra* Extract | Glycyrrhizin | Gravimetric |
| *Zingiber officinale* Extract | Gingerol | HPLC |
| *Asparagus racemosus* Extract | Saponins | Gravimetric |
| Ashwagandha  Extract | Total Withanolides | Gravimetric |
| *Tinospora cordifolia* Extract | Bitters | Gravimetric |
| *Piper longum* Extract | Piperine | HPLC |
| *Embelia ribes* Extract | Embelin | HPLC |

Placebo is composed of: Maize starch 40%, DCP (dicalcium phosphate) 40% and magnesium stearate 20%

## Preclinical experience

There are studies done and literature available on almost each of the component of Cap. IP.

## (b) Clinical experience

There are studies done and literature available on almost each of the component of Cap. IP. The dose of each component in the IP is very safe to administer. The investigational products are in use since more than 6 months in various health conditions.

Various references on safety of individual ingredients of the formulation:

1. ***Haritaki (Terminalia chebula)***

Mutagenicity and oral toxicity studies of *Terminalia chebula*

<https://pubmed.ncbi.nlm.nih.gov/21538627/>

Safety assessment of methanolic extract of Terminalia chebula fruit, Terminalia arjuna bark and its bioactive constituent 7-methyl gallic acid: In vitro and in vivo studies

<https://www.sciencedirect.com/science/article/abs/pii/S0273230017304063>

Acute and chronic toxicity studies of the water extract from dried fruits of *Terminalia chebula* Rezt. in rats

<http://citeseerx.ist.psu.edu/viewdoc/download?doi=10.1.1.980.5655&rep=rep1&type=pdf>

Evaluation of Toxic Effect of *Terminalia Chebula* Fruit Extract in Albino Rats

<http://www.ijpsi.org/Papers/Vol7(4)/E0704012836.pdf>

# Study Rationale

COVID -19 is a respiratory illness that has led to a pandemic, affecting more than 200 countries in the world. Due to sudden advent and rapid spread of infection, no antiviral drug has been found to be effective since its onset.

1. While there is no medicine for COVID-19 as of now, enhancing the body’s defense system (immunity) plays an important role in maintaining optimum health and the IP (study drug) might possibly play an important role in enhancing immunity.
2. Role of study drug as an antiviral could also be tested.

The proposed trial is to check efficacy of Cap. IP in the management of COVID-19.

We intend to enroll up-to 75 COVID positive patients in the study. Eligible and willing patients will either get Cap. IP as an add-on therapy to the SOC (Standard of Care) or placebo (inert substance) as an add-on therapy to the SOC.

Aim: To assess the efficacy and safety of Cap. IP in the management of COVID 19 patients and also in boosting innate immunity.

# Study Objective(s)

## Primary Objective

- To assess the efficacy of herbal extracts in boosting innate immunity of patients with COVID-19 infection.

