## Secondary Objectives

- To assess the efficacy of herbal extracts in restoring respiratory health
- To assess the efficacy of Cap. IP in early recovery of patients and decline in v iral l oad
- To assess the safety of herbal extracts

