- Efficacy of the herbal extracts in COVID 19 positive patients (in declining viral load: time-point: 5 days and early recovery)

Secondary Outcomes:

- - Efficacy of the herbal extracts as an immune-modulator - TH1, TH2, Th17, IL6, NK Cells and CD markers; Immunoglobulin IGG (Serum); Immunoglobulin IGM (Serum): at 30 days.
  - Efficacy of the investigational product in reducing sequela of the disease
  - Safety analysis (Liver Function Test and Kidney Function Test) including serious allergic reaction of: rash, itching/swelling, severe dizziness, trouble breathing.

1. Details about the Investigator*

Name

Address

Telephone number

Profession (specialty)

Date of reporting the event to Ethics Committee:

Signature of the Investigator

Information marked ‘*’ must be provided.

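### The primary objective (innate immunity) and the primary outcome (day-5 viral load and early recovery) contradict each other, and the primary outcome joins two endpoints with no success rule

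*Protocol*

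**What the plan says.** Under Study Objective(s), the Primary Objective has a single entry: "To assess the efficacy of herbal extracts in boosting innate immunity of patients with COVID-19 infection". One of the Secondary Objectives is "To assess the efficacy of Cap. IP in early recovery of patients and decline in v iral l oad" (the broken spacing comes from text extraction).

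The outcome lists come later, inside the adverse-event reporting format under Study Treatment. The entry under Primary Outcome is "Efficacy of the herbal extracts in COVID 19 positive patients (in declining viral load: time-point: 5 days and early recovery", with the bracket closing there. The first entry under Secondary Outcomes is "Efficacy of the herbal extracts as an immune-modulator - TH1, TH2, Th17, IL6, NK Cells and CD markers", followed by serum IgG and IgM, all at 30 days.

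Four other places bear on which of these leads:

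- The aim in the Study Rationale is "To assess the efficacy and safety of Cap. IP in the management of COVID 19 patients and also in boosting innate immunity".
- The sample size table in Methods and Procedures compares 5% with 35% for an outcome that it does not name. The text just before it justifies the size by a paired t test.
- Data Analysis provides for a paired t test and any other suitable test, and names no endpoint.
- Study Design describes the trial as exploratory.

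**The concern.** The objectives and the outcomes rank the same two topics in opposite order. Which endpoint is primary cannot be a detail left to a statistical analysis plan, because the protocol has already stated it in two conflicting ways. Any analysis plan would have to contradict one of the two sections.

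The primary outcome is also loose in itself. It links viral load and early recovery with *and*, without saying whether success needs one or both. Only viral load has a time point.

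What is at stake is the reading of the result. Once the blind is broken, whichever of the viral-load, recovery or immune results looks best could be put forward as primary, with protocol text to support it.

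**Working it through.** **Step 1. Set the sections side by side.**

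| Topic | Objectives | Outcome lists |
| --- | --- | --- |
| Immunity | Primary (innate immunity) | Secondary (immune markers, day 30) |
| Viral load and early recovery | Secondary | Primary (viral load at day 5; recovery undated) |

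Both columns are current text, and the order is fully reversed.

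**Step 2. Look for a section that settles it.** The aim joins both topics without rank. Data Analysis names no endpoint. The paired t test given as the reason for the sample size is a within-patient test on a continuous variable, and it is not linked to any endpoint. That leaves the sample size table.

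**Step 3. Reproduce the sample size.** Inputs from the table: 5% against 35%, two-sided 5%, 80% power, ratio 1. Hence p̄ = 0.20, d = 0.30, z = 1.960 and 0.842.

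- Fleiss, no continuity correction: n = [1.960·√(2·0.20·0.80) + 0.842·√(0.05·0.95 + 0.35·0.65)]² / 0.30² = 26.7, so 27 per arm and 54 in total. This matches the table.
- Kelsey: n = (1.960 + 0.842)²·2·0.20·0.80 / 0.30² = 27.9, so 28 per arm and 56 in total. This matches the table.

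The arithmetic is sound. It does not resolve the conflict, because the 5% and 35% are tied neither to viral load, nor to early recovery, nor to an immune marker.

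**Step 4. Read the *and* in the primary outcome both ways.** This is an illustration. It assumes two independent components, each tested at 5%.

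- Either component suffices: chance of at least one false positive = 1 − 0.95² = 0.0975, or 9.8%.
- Both are required: a false claim needs at least one ineffective component to reach significance, so the rate does not exceed 5%. The price is power. If each component had the 80% in the table, joint power would be 0.80 × 0.80 = 0.64.

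If either sufficed and the 5% were split equally, and if 5% against 35% applied to both components, the Fleiss formula at 2.5% gives 33 per arm instead of 27. At the flow chart's 30 per arm, power would be 76.3%, against 84.6% for one test at 5%. The two readings are therefore different trials, and the protocol does not say which one is planned.

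**The case against.** The strongest reply is that the protocol does name a primary outcome, dates its viral-load component at 5 days and labels the immune markers secondary. The trial also calls itself exploratory, and multiplicity rules and the detailed definition of recovery may sit in an analysis plan that is not shown. Much of this stands. It limits how far the point can be taken, but it does not remove the contradiction, since the immune route to a primary claim rests on an equally explicit label in the objectives.

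Several stronger readings are tempting, and the documents do not support them.

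- *The trial has no question on which it can succeed or fail.* That applies a confirmatory standard to a trial described as exploratory.
- *The false-positive risk is 34% or more.* The figure is 1 − 0.95⁸ for the eight listed immune items. It assumes independence, although several items come from one lymphocyte panel on the same blood, and it concerns markers labelled secondary. Correlation would lower it and splitting the CD markers into separate tests would raise it, so the direction of the error is unknown.
- *The innate components named in the background are not measured.* The Symptomatology section says "Epithelial cells, alveolar macrophages and dendritic cells (DCs) are three main components for innate immunity in the airway". That is background on the airway, not a definition of the endpoint for a blood-sampling study. The protocol does not classify its markers as innate or adaptive either.
- *Recovery can be observed only at days 5, 15 and 30.* Those are the scheduled contacts, but continuing physician visits are expected and the case record form is not shown, so a recovery date might be captured.

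**Conclusion.** The contradiction is literal and nothing elsewhere in the protocol resolves it. It should be corrected before unblinding, because the interpretation of the main result depends on it. The exploratory label softens the consequence but does not excuse it: the protocol still declares a primary objective, a primary outcome and a sample size with 80% power.

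The finding rests on wording and needs no numerical assumption. The 9.8% is conditional on an either-component rule, independence and 5% per component, and under a both-components rule it does not apply. No corrected sample size follows until one endpoint has been chosen.

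**What to change.** Before unblinding, name one primary endpoint by variable, time point and between-arm comparison, and make the primary objective, the primary outcome and the sample size basis agree with it. The choice is the sponsor's.

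- **Primary.** The natural candidate is the between-arm difference in log10 viral load at day 5, adjusted for day 0. It is the only primary component with a stated time point, and Study Design plans quantitative RT-PCR on all subjects at that visit. Confirm that the day-0 test is quantitative: the Study Assessment Table implies it, while the day-0 entry in Study Design says only RT-PCR.
- **Early recovery.** Make it secondary, with a definition that the planned contacts can supply, for example recovered by day 5 and by day 15, yes or no.
- **Immune markers at day 30.** Make them a secondary objective with a stated favourable direction for each. The protocol's own background shows why direction matters: "The more severe conditions patients were in, the higher their IL-6 levels were". That statement comes from mainly severe cases, so it shows that a direction is needed but does not settle which one applies in mild to moderate disease.
- **Sample size.** Tie the 5% and 35% to the chosen endpoint or replace the justification. For a continuous endpoint with 30 per arm, 80% power corresponds to a difference of (1.960 + 0.842)·√(2/30) = 0.72 standard deviations, before any gain from baseline adjustment. The sponsor would have to judge whether that difference is plausible.

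The cost is a protocol amendment and a re-justified sample size. If day-0 quantification is confirmed, no new measurement is needed. The sponsor gives up one of its two headline claims.

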## Secondary Objectives

- To assess the efficacy of herbal extracts in restoring respiratory health
- To assess the efficacy of Cap. IP in early recovery of patients and decline in v iral l oad
- To assess the safety of herbal extracts

# Study Design

Overview of the Study Design

- This is a randomized, 2-arm, parallel group, double-blind, 1:1 ratio, controlled, exploratory trial with a study period of 30 days from the of enrolment.
- A total of up-to 75 known COVID-19 positive (with positive RT-PCR) patients will be enrolled in the study.
- All the patients enrolled in the study will get the Investigational Product (IP-1 and IP-2), or 2 capsule of Placebo in similar sized and colored bottles, two times daily for the 1^st^ 15 days. From 16^th^ day onwards patients will get one capsule twice daily i.e. IP-2 or capsule placebo up to day 30.
- Patients will undergo laboratory investigations upon enrolment and on last visit. RTPCR for COVID will be done on day 5 (+ 1 day).
- Patients and doctors treating will not be knowing what the participating subject has received. Subjects will be given coded bottles, containing dose for 30 days.
- No medicine which his/her physician is giving will be stopped. No modifications shall be suggested in their diet and daily routine physical activities.
- Thus, patients enrolled in the study will get the IP / Placebo in addition to the standard of care which they were already receiving at the time of enrolment.
- Half of patients will be getting Cap. IP and half will be getting Cap. Placebo throughout the study duration of 1 month.

Study period for enrolled patients will be 30 days:

- Enrollment (day 0): After Informed Consent Process, Demographics and other information for CRF will be recorded. Investigations: COVID 19 RTPCR, Lymphocyte subset analysis (TH1, TH2, Th17, IL6, NK Cells and CD markers); Immunoglobulin IGG (Serum); Immunoglobulin IGM (Serum); Liver Function Test and Kidney Function Test will be done. Cap. bottle will be given to the patients with the dose lasting for 30 days.
- Day 3±1: COVID-19 RT PCR (quantitative) test will also be conducted on day 3 (±1) on 5 subjects of each group
- Follow-up 1: Day (5±1): COVID-19 RT PCR (quantitative) test will be conducted for all subjects on Day (5±1). CRF will be filled for knowing the overall status.
- Follow up 2 (15^th^ day+ 2 days): This follow up will be clinical/telephonic. CRF will be filled for knowing the overall status.
- Follow up 3 (30^th^ day+ 2 days): Patients will be followed up at day 30. This visit will be done telephonically. Patient will not visit site but blood investigations shall be carried out. Investigations will be done outside the site, considering that the site is COVID specific hospital. The investigations are; Lymphocyte subset analysis (TH1, TH2, Th17, IL6, NK Cells and CD markers); Immunoglobulin IGG (Serum); Immunoglobulin IGM (Serum); Liver Function Test and Kidney Function Test will be done. All the unused IP will be collected.
- Sponsor will provide 10 codes (5 from each, IP and placebo, not mentioning which is placebo and IP). These will get Sr. Ferritin, CRP and D- Dimer done for same patients on day 0.

Every time subject coming to the scheduled follow-up should be asked to bring the remaining capsules with the bottle.

Flow chart

Screening

(I/E Criteria, ICF reading)

Enrollment (Day 0) Randomization

IP Arm Placebo Arm (30 patients in each arm)

(Consenting, Clinical Exam, Investigations, QOL, IP / Placebo Dispense)

COVID-19 RT PCR (quantitative) test on day 3 (±1) for 5 subjects of each group

1^st^ Follow-up: Day (5±1)

COVID-19 RT PCR (quantitative)

2^nd^ Follow-Up: Day (15+2)

[Clinical/telephonic]

3^rd^ Follow-Up: Day (30+2)

[Tele follow-up Blood Investigations at lab]

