# **Methods and Procedures**

Patients attending COVID treatment center (YCM Hospital, Pimpri, Pune, India) of the investigators will be screened for their participation in the study. Patients should be COVID-19 positive, diagnosed recently. No discretion for enrollment will be made based on gender, color, religion and cast. Information about the study will be shared with the patients and their eligibility will be checked during screening. Those fulfilling this requirement and who are willing to participate will be given informed consent document and patient information sheet for reading. Adequate time will be given for reading the same and the same will be explained verbally. All questions will be answered to the patients’ satisfaction. Patient will be considered as enrolled only after consenting procedure is done.

Patients will be counseled about administration of IP (dose, timing, method etc.). In case of SAE / other event which necessitates to break the blind, it will be broken. Appropriate treatment will be provided and the IP might be discontinued if investigator thinks this in the best health interest of the participant.

Follow-Up:

After enrollment (Day 0), there will be one clinical and the next two: either telephonic or clinical follow-ups: first follow-up visit at day 5 (+1 day), second follow-up visit at day 15 (+2 days) and third follow-up visit at day 30 (+2 days).

Patients will need to make sure, there is no gap in consuming the IP.

Patients can call the study coordinator anytime for the queries if any.

Unscheduled Visits:

Patients will continue to visit his/her physician at the site for medical care with prior appointments for routine and regular check-ups. Study coordinator will try and combine their study follow-up visit with their regular visit at the site. Patients should, as far as possible, visit the site in case of medical emergencies.

Study Design:

This is a two arm, double blind, randomized, controlled, prospective study to determine safety and efficacy of Cap. IP in COVID-19 positive patients.

After enrollment, they will get the IP / Placebo in addition to their regular treatment they might be receiving for their condition. (2 capsules twice a day for prior 15 days and 1 capsule twice a day from day 16)

A total of 60 patients (Can be extendable to 150) will be enrolled in the study in different groups. The reason behind this sample size that, we can apply paired t test with adequate power for an exploratory study.

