# Study Assessments:

Participants will have a minimum of two follow-ups. Clinical assessment will be done; vitals will be noted, questionnaire will be filled-in and blood will be collected for various parameters.

Study Conduct:

Patients screened, eligible and willing will be enrolled in the study and IP will be dispensed. During screening, inclusion-exclusion criteria will be applied. Those fulfilling the criteria will be given detailed information about the study. Of those who are willing to participate will be asked to sign the informed consent form. Study coordinator with the principal or co-principal investigator will participate in the consent process.

Day of consenting will be done on the day of screening. After signing the consent form, on enrollment day, physical examinations will be done; blood will be withdrawn for investigations, case record form will be filled and IP will be dispensed. A copy of duly signed informed consent form will be given to them.

Follow-up Visit 1 [5^th^ day (+ 1) of the day of enrollment]: Questions will be asked about adherence, missed doses if any and adverse events if any. NP swab will be collected for RT-PCR of COVID-19

Follow-up Visit 2 [15^th^ day (+ 2) of the day of enrollment]: All the procedures for this visit will be the same as that of Visit 1, except that swab will not be collected for RT PCR.

Follow-up Visit 3 [30^th^ day (+ 2) of the day of enrollment]: All the procedures for this visit will be the same as that of Visit 2, and in addition, blood will be drawn for various markers.

Discontinued Patients:

Patients will be withdrawn/dropped from the study if they violate the protocol e.g. by participating in other study, by not taking the IP, not coming to the hospital for follow-up etc. Patients developing any serious disease, patients wanting to withdraw will also be withdrawn from the study.

Patients who have not turned for clinical follow-up will be called telephonically up to three times after the window period is over. During consenting they will be asked if it is alright with them.

However, as it is a ‘intent-to-treat’ (ITT) study design, data collected of such patients, till they are dropped out/withdrawn from the study will be included in the analysis.

Patients will be insisted to visit during the window-period. Those who miss this will still be continued into the study. On case-to-case basis, protocol waivers will be granted by the co-PI and/or the PI.

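### The day-5 viral-load swab has two collection windows, ±1 day and +1 day, so day 4 is both in and out of window and can overlap the day-3 sub-study swab

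*Protocol*

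**What the plan says.** The Primary Outcome entry of the protocol defines efficacy as "in declining viral load: time-point: 5 days and early recovery". Day 5 is the only time point given for viral load.

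The swab that supplies it is scheduled in six places.

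- **±1 day.** The Follow-up 1 bullet in Study Design: "COVID-19 RT PCR (quantitative) test will be conducted for all subjects on Day (5±1". The flow chart in the same section: "Follow-up: Day (5±1".
- **+1 day.** The overview bullet in Study Design: "RTPCR for COVID will be done on day 5 (+ 1 day". Methods and Procedures: "first follow-up visit at day 5 (+1 day". Study Assessments, which describes the visit at which the nasopharyngeal swab is taken: "Follow-up Visit 1 [5^th^ day (+ 1) of the day of enrollment". The column heading for the first follow-up in the Study Assessment Table also gives +1.

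A sub-study adds an earlier swab: "COVID-19 RT PCR (quantitative) test will also be conducted on day 3 (±1) on 5 subjects of each group". The flow chart and the footnote to the Study Assessment Table repeat that ±1 window.

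On missed windows, Study Assessments keeps the patient in the study and lets the investigators grant waivers case by case. Data Analysis says that all collected data will be analysed, and it names a paired t test and any other appropriate test.

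**The concern.** Site staff follow the protocol's collection window, and here it is stated two ways for the measurement behind the primary outcome. Under one version a swab taken on day 4 is on schedule. Under the other it is early. In a sub-study patient, a day-4 swab also fits the day-3 visit under the ±1 version, and no rule says which time point it then serves.

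Viral load is expected to change from day to day during recovery. A wider spread of sampling days therefore adds variation to the day-5 result that has nothing to do with treatment. At stake are a little precision and an unambiguous definition of which swabs belong to the primary time point. The sample size and the type I error rate are not affected.

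**Working it through.** **The plan's own figure.** The sample-size table uses 5% v 35%, two-sided 5% significance, 80% power and 1:1 allocation. It reproduces.
- Kelsey: (1.960 + 0.842)² × 0.20 × 0.80 × 2 / 0.30² = 27.9, so 28 per arm and 56 in total.
- Fleiss without continuity correction: 27 per arm and 54 in total.

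The point does not depend on these figures.

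**Windows as sets of days.**

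| Source in the protocol | Stated window | Days allowed |
| --- | --- | --- |
| Study Design, Follow-up 1 bullet | 5 ±1 | 4, 5, 6 |
| Study Design, flow chart | 5 ±1 | 4, 5, 6 |
| Study Design, overview bullet | 5 +1 | 5, 6 |
| Methods and Procedures | 5 +1 | 5, 6 |
| Study Assessments | 5 +1 | 5, 6 |
| Study Assessment Table | 5 +1 | 5, 6 |
| Sub-study swab | 3 ±1 | 2, 3, 4 |

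The two day-5 versions differ only on day 4. The sub-study window shares day 4 with the ±1 version and no day with the +1 version. Both symbols occur within Study Design, and both again within the Study Assessment Table and its footnote, so a sign lost in text extraction is an unlikely explanation.

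**Patients the overlap can touch.** The sub-study has 5 subjects in each group, so 10. That is 10/60 = 17% at the flow chart's 30 per arm and 10/75 = 13% at the stated maximum of 75. It is a ceiling: the overlap arises only if a sub-study patient is actually swabbed on day 4.

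**Effect on outcome variance.** The documents give no rate of decline, SD or distribution of swab days. Assumptions: slope b = 0.2–0.5 log10 per day, SD = 1.5–2.0 log10, and swab days spread evenly over the allowed days.

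- Variance of swab day over {4, 5, 6}: (1 + 0 + 1)/3 = 0.667.
- Variance of swab day over {5, 6}: 0.5² = 0.25.
- Added variance as a fraction of outcome variance = b² × Var(day) / SD².

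| | b = 0.2, SD = 2.0 | b = 0.5, SD = 1.5 |
| --- | --- | --- |
| ±1 window | 0.04 × 0.667 / 4 = 0.7% | 0.25 × 0.667 / 2.25 = 7.4% |
| +1 window | 0.04 × 0.25 / 4 = 0.3% | 0.25 × 0.25 / 2.25 = 2.8% |
| Difference (before rounding) | 0.4% | 4.6% |

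Only the last row is attributable to the wider window, because some spread remains under +1.

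**The same noise seen as chance imbalance.** With 30 per arm, the difference between arms in mean swab day under ±1 has SD √(2 × 0.667 / 30) = 0.21 day, equivalent to 0.04–0.11 log10. This restates the variance above and is not a further effect.

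**The case against.** The strongest reply is that this is an editorial slip with little consequence. Patients who miss the window stay in the study, and all collected data are analysed, so nothing in the protocol makes window status a ground for discarding a swab. The trial is double-blind and nothing suggests that swab timing would differ by arm. The day-3 test is described as additional to the all-subject test, so two swabs are planned and not one swab counted twice. Analysis windows and covariates may be set in a statistical analysis plan that is not shown. Most of this stands, and it limits the point to a small one.

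It does not remove the contradiction. An analysis plan can decide how a swab is used, but the collection window that sites work to is the protocol's own, and it reads two ways.

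A reader might infer more than the documents support:

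- **That a day-4 swab is a protocol deviation.** The protocol does not label out-of-window swabs, so only in and out of window can be said.
- **That day-4 swabs could be dropped once results are known.** The text on missed windows and on analysing all data points the other way.
- **That the arm comparison is biased.** No mechanism that differs by arm is shown.
- **That nothing will account for sampling day.** This protocol specifies no adjustment, but that is commonly left to the analysis plan.

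**Conclusion.** The protocol contradicts itself on the collection window for its day-5 viral-load swab, and one day, day 4, has no settled status. Under the assumed slope, SD and even spread of swab days, the wider window costs about 0.4–4.6% of outcome variance compared with +1. The top of that range needs the steepest slope and the smallest SD together. The overlap with the sub-study exists only under ±1 and can touch at most 10 patients. The point is worth correcting for clarity and does not threaten the trial's conclusions.

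Calling viral load primary follows the Primary Outcome entry. Study Objective(s) lists decline in viral load among the secondary objectives, which is a separate inconsistency.

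**What to change.** - State one window in every place. Day 5 (+1) is the majority wording, matches the Study Assessment Table and shares no day with the day-3 window. Only the Follow-up 1 bullet and the flow chart in Study Design would change.
- Record the date of each swab. The protocol does not say that it is captured.
- State that all day-5 swabs stay in the analysis whether or not they fall in window, as Study Assessments and Data Analysis already imply.
- State that one swab serves one time point only.
- Compare day-5 viral load between arms adjusting for the day-0 RT-PCR value, which is already collected.
- Use actual swab day only in a sensitivity analysis. It is determined after randomisation, and if recovery or discharge influences when patients are swabbed, adjusting for it could distort the comparison.

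The cost is wording in two places, one date field and a sentence on analysis. A narrower window will put slightly more swabs out of window, but they remain in the analysis.
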